### Sample size

Power analysis (G-power) was conducted based on a 12-month effect size of .20. Although the expected effect size for a depression prevention program for high-risk youth is .40 (based on research of [11]; see also [3], the formulated effect size is more conservative, because the intervention will be conducted in classes of approximately 25 adolescents per class instead of 10 to 15 adolescents per group - as is done in some other school-based prevention programs [1]. For the power analysis, we considered potential loss of power due to clustering of data in groups at schools and due to multiple imputation and testing of mediational mechanisms. A maximum of 20% attrition over time has been taken into account as well. The sample sizes need to be 662 students per condition (alpha < .05, power = .80) and therefore the total sample size at baseline was determined to include 1,324 participants.

### Intervention

The OVK program will be taught by intensively trained school teachers and covers cognitive-behavioral and social problem-solving skills. Within 16 lessons of 50 minutes that are delivered during school hours, adolescents learn to detect inaccurate thoughts, to evaluate the accuracy of those thoughts, and to challenge them by considering alternative interpretations. They also learn techniques for assertiveness, negotiation, decision-making, social problem-solving and relaxation. The skills in the program can be applied to many contexts of life, including relationships with peers and family members as well as achievement in academics or other activities. Details about the content of the program are described extensively elsewhere [5]. To be able to deliver the program, the school teachers of the classes in the intervention condition will receive a 4-day training by two staff members of the research group; both of them are experienced and licensed psychologists and both are experts in cognitive behavioral therapy. The teachers receive a detailed manual of the program as guideline and they have the option to contact the trainers for additional support during program delivery.

### Assessments

The primary outcome is the level of symptoms of depression and will be measured with the Children's Depression Inventory (CDI) [23], which has been used in the vast majority of RCTs on universal depression prevention programs for youth and has good internal consistency and convergent validity [24]. The possibly mediating factors are cognitive errors, response style, attributional style, and alexithymia. The Children's Negative Cognitive Errors Questionnaire - Revised (CNCEQ-R) [25] will be used to measure five empirically derived negative cognitive error categories and is a revised version of the CNCEQ [26], which has a good internal consistency and test-retest reliability. The response style is measured with the Children's Response Styles Questionnaire [27] and consists of three subscales with moderate levels of internal consistency: ruminative response, distracting response and problem-solving. A shortened version of the Adolescent Cognitive Style Questionnaire [28] is used to measure attributional style. Adolescents rate the degree to which the cause of a hypothetical negative event is internal, stable and global. The scale has an excellent internal consistency and good test-retest reliability. Alexithymia is assessed with the subscales 'having difficulty identifying feelings' and 'having difficulty describing feelings' of the Toronto Alexithymia Scale (TAS20) [29,30] with good internal consistency and test-retest reliability.

Secondary outcomes are stressful life events, substance use, happiness, and school grades. The Adolescent Life Events Questionnaire - Revised [31] is used to assess the occurrence of a broad range of negative events which are typically reported by adolescents. The internal consistency of the scale is satisfactory. The Cantril Ladder will be used to measure happiness [32]. Academic performance will be assessed objectively by school grades we will receive from the schools. Socio-demographic variables of the adolescents and their family will be obtained by questions about sex, age, educational level, ethnicity, religious affiliation and psychiatric problems of the parents. The frequency and intensity of alcohol and tobacco use will be measured through commonly used questions that assess use of these substances [33-36].

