## Methods/Design

### Design

The present longitudinal study involves a randomized controlled trial (RCT) with two conditions (intervention versus control) (see Figure 1) in which the effectiveness and the underlying mechanisms of the Dutch school-based depression prevention program Op Volle Kracht will be examined among adolescents from low income areas. The adolescents in the classes that will be assigned to the intervention condition will receive the 16-week OVK program from their teacher. Adolescents in the control condition will receive the usual school curriculum. While alternative interventions to control for nonspecific intervention ingredients are included in some of the PRP studies [4], the approach of 'care as usual' is chosen in the present study because no other school-based depression prevention program is currently implemented in the Netherlands. Still, some schools do provide social skill programs and we did not forbid schools to conduct those programs. The extent to which participants are involved in other prevention programs during the course of the study will be registered.

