### Participants and procedure

All the secondary schools in the Netherlands that meet the criterion of having at least 30% of their pupils inhabiting low income areas will be approached for participation in the study. In the Netherlands, this information can be obtained from the Dutch Ministry of Education, Culture and Science and it is based on the average income in the postal code area in which the pupils live. The eligible schools are predominantly situated in urban areas. Two other selection criteria are the educational level and age: pupils from vocational training up to pre-university level and from the 7^th ^and 8^th ^grade (range 11 to 14 years old) are selected. Two weeks after approaching the school by means of a written invitation, they will be contacted by telephone. If they are interested in participating in the study, a personal visitation will follow and classes will be selected. From the participating classes, none of the pupils will be excluded, to avoid stigmatization and social exclusion. With support from the schools, all parents will receive a letter to inform them about the content and aim of the program as well as the procedures of the study. Permission from the parents for their child's participation will be obtained through informed passive consent. If parents do not give permission for participation in the study, the adolescents will still attend the OVK program because it is taught in the regular school curriculum, but no data will be collected from them. To protect confidentiality of the data provided by the participating adolescents a unique code will be assigned to each participant. The Ethical Committee of the Faculty of Social Sciences at the Radboud University Nijmegen approved the study's protocol.

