### Randomization

The classes will be randomly assigned to two conditions (intervention or control). An independent researcher will perform the allocation before the baseline assessment will be administered. Randomization will be carried out centrally on class-level and within schools to control for school characteristics, using a computerized random number generator with blocked randomization scheme (block size 2) and stratified by level of education (high versus low).

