### Strengths and limitations

One of the strengths of this study concerns the rigorous research design of a randomised controlled trial with a large sample (N = 1,324) to analyse the underlying mechanisms and the sequence of change in the parameters. Another strength is the assessment of the cognitive distortions as possible mediators of symptoms of depression, which are based on three well-established cognitive theories [13-15]. Further, the added construct alexithymia has not yet been studied thoroughly in combination with depressive symptoms in youth. In addition, other highly relevant outcomes, such as academic achievement, will be measured to evaluate if other effects besides stimulating mental health might be reached by this program. Further, all assessments will be completed during school hours, which will ensure low attrition rates. An additional strength of the study is that the program will be delivered by teachers in a school setting, because the results will be of great importance in the discussion about practical implementation under real-world conditions (see also [1]). Last, the schools that will be participating in the study have a high diversity in school characteristics, e.g. Christian, Islamic, which generates a good external validity for the results of the study.

On the other hand, several limitations of this study exist. First, probably primarily motivated schools will join in the study, which may limit generalizability of the results to all schools. Second, by using a within-school design (as opposed to a between-schools design), contamination effects between the experimental and the control group could occur, although we expect to minimize these effects by delivering the program to entire classes instead of parts of classes. Third, the measurements are solely based on self-reports. Nevertheless, with respect to internalizing problems, it has been shown that adolescents are probably better informants compared to their parents or teachers [42]. At last, no integrity check of the delivery of the program will be conducted because of financial restrictions. However, the teachers will report on program adherence by filling out forms through which they report which (part of the) lessons they have covered.

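### School grades are called an objective outcome, but they come from schools whose unblinded teachers deliver the programme, so a grade difference may partly reflect the grader

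*Protocol article*

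**What the plan says.** The Assessments section places grades among the secondary outcomes: "Secondary outcomes are stressful life events, substance use, happiness, and school grades". It then characterises them: "Academic performance will be assessed objectively by school grades we will receive from the schools".

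On who delivers the programme, the Design section says: "The adolescents in the classes that will be assigned to the intervention condition will receive the 16-week OVK program from their teacher". The comparator is described in the next sentence: "Adolescents in the control condition will receive the usual school curriculum". The Intervention section adds that "the school teachers of the classes in the intervention condition will receive a 4-day training".

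On the range of pupils, Participants and procedure admits "pupils from vocational training up to pre-university level". On allocation, the Randomization section says: "Randomization will be carried out centrally on class-level and within schools to control for school characteristics". Blocks are of size 2 and there are two strata of education level. The Statistical analysis section compares the arms at baseline, school level included, and enters into the effectiveness models those variables that turn out to differ. Standard errors are corrected for clustering by class.

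Strengths and limitations presents academic achievement as a way to show effects beyond mental health. Among the limitations it states: "Third, the measurements are solely based on self-reports".

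**The concern.** Calling an outcome objective tells the reader that the assessor's knowledge of the allocation cannot move it. A mark awarded by a teacher does not have that property unless the marking is masked or external. Here the teaching staff include people who were trained for the intervention arm only and who delivered the lessons. If any of them also mark the pupils, a more generous or more attentive grader in one arm would look like an academic benefit, in the only outcome the article presents as objective.

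A second, smaller matter is the scale. A mark in a vocational class and the same mark in a pre-university class refer to different content and standards. Pooling them without regard to level adds variation that has nothing to do with the programme.

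**Working it through.** The article gives no figure for grades, so there is none to reproduce. The check is a comparison of the text, followed by two illustrations under stated assumptions.

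**1. The text side by side**

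- Source of grades: the schools (Assessments).
- Who knows the allocation: at least the teachers of intervention classes, since they are trained for the programme and teach it (Design, Intervention).
- Do these teachers work with pupils outside the OVK lessons? Implications for practice expects them to carry their skills into other parts of the curriculum, which suggests that they do.
- Who awards the counted grades, and is marking masked or external? The article does not say who, and describes neither safeguard.
- Limitations: all measurements are called self-report. School-supplied grades are not, so this sentence and the Assessments section contradict each other. The source of bias specific to grades is not named.

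**2. What a marking shift would do (illustration)**

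Inputs from Sample size: effect size 0.20, power 0.80, 662 per arm, 20% attrition. Two-sided alpha of 0.05 is assumed, because the article does not give the sidedness.

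- Unclustered n per arm: 2 × (1.96 + 0.84)² / 0.20² ≈ 393.
- Retained per arm: 662 × 0.8 = 529.6.
- Implied design effect: 529.6 / 393 = 1.35. This assigns the whole margin to clustering, which is an assumption. The article states no intraclass correlation and also mentions imputation and mediation testing.
- Effective n per arm: 529.6 / 1.35 ≈ 393. The standard error of the standardised difference is √(2/393) = 0.0713.
- With no true effect and a marking shift b in the intervention arm, the chance of a significant benefit is 1 − Φ(1.96 − b/0.0713).

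| Assumed shift b (SD) | b / 0.0713 | Chance of a significant benefit |
|---|---|---|
| 0.05 | 0.70 | about 10% |
| 0.10 | 1.40 | about 29% |
| 0.20 | 2.81 | about 80% |

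The nominal chance in that direction is 2.5%. The values of b are assumed. If grades cluster more strongly within classes than this design effect implies, the percentages are lower. Randomisation and the cluster correction do not remove a shift that arises after allocation in one arm.

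**3. What education level would do (illustration)**

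Assume about 52 classes (1,324 / 25 ≈ 53), allocated as 26 pairs. Assume also two equally common sub-levels inside a stratum, whose grades differ by g SD. Each pair contributes an imbalance of −1, 0 or +1 with mean 0 and variance 0.5. The arm difference due to level therefore has mean 0 and SD g × √(26 × 0.5) / 26 = 0.139g.

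- g = 0.25: SD about 0.03.
- g = 0.5: SD about 0.07.
- g = 1.0: SD about 0.14.

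A simulation of 20,000 allocations gave the same SDs and a mean of 0.00 for each g. Level therefore adds noise of the same order as the standard error in step 2, and no systematic shift.

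**The case against.** The strongest reply has four parts.

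- **Wording.** In context, *objectively* may only contrast school records with the pupil questionnaires. That is a fair reading of the intent, but the word still claims more than school-awarded marks can support.
- **Grader identity.** A reader might infer that marks given by the OVK teacher certainly enter the outcome. The article does not say so, and a teacher who marks both arms could dilute any shift. It is a risk, not a documented fact.
- **Education level.** A reader might infer that the mix of levels could favour one arm. The document does not support that. Classes are randomised within school and stratified by level, and level is adjusted for if it differs. Only the loss of precision stands.
- **Detail and size.** The choice of subjects and the scaling of grades are details that an article may leave to the full protocol or analysis plan. Their absence is not the fault raised here. The faults are the claim of objectivity, the contradiction over self-report, and a stated rule that adjusts for level only when it happens to differ. It is also true that no marking shift, and no OVK teacher's share of the grade average, can be taken from the document. A bias quoted as a share of 0.20 would moreover use the effect size that powers the depression trial, since no expected effect on grades is given.

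**Conclusion.** The point holds in a limited form. The claim that grades are an objective measure is unsupported: they come from schools in which unblinded staff deliver the programme, and no masked or external marking is described. A grade difference may partly reflect the grader. The self-report sentence in the limitations contradicts the use of school-supplied grades, whatever the size of any bias.

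The size of a marking bias is unknown. The 10%, 29% and 80% figures show only how sensitive the result would be, and they rest on the assumed shifts, 80% retention and a design effect of 1.35. Level costs precision (a chance SD of 0.03 to 0.14 under the assumed gaps) and does not favour an arm.

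Grades are a secondary outcome. The conclusion on the Children's Depression Inventory is unaffected. The change is worth making because it is cheap and because the article offers academic achievement as a further benefit of the programme.

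**What to change.** 1. **Main analysis of grades.** Compare arms within school and education level. Either standardise grades within school, level and subject, pooling both arms, or always include the strata in the model, whether or not level differs at baseline. Adjust for the pre-programme grade where the school supplies it.
2. **Sensitivity analysis.** Drop subjects marked by a teacher who delivered OVK, and remove the same subject from both arms in that school and level. Dropping it from intervention classes alone would leave the two averages resting on different subjects and could create an arm difference of its own.
3. **Assessments.** Delete *objectively*.
4. **Strengths and limitations.** Correct the sentence on self-report so that it excludes grades, and list possible grader awareness of allocation as a limitation.

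The cost is some rewording, a request to schools for grades by subject with a note of which teacher marked them, and a narrower grade average in the sensitivity analysis. A school-by-level stratum with classes in only one arm adds nothing to the within-stratum comparison.

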### Statistical analysis

Data will be analyzed in accordance with the intent-to-treat principle but will also be analyzed separately for the completers only. Multiple imputations will be used for missing observations at follow-ups. The hypotheses will be tested with regression analyses for dichotomous and linear outcome measures in MPLUS 5.1 [37]. We will check for possible baseline differences between the two conditions in demographic variables (e.g. age, sex, school level, and ethnic background) and depressive symptoms. Moreover, variables that show different distributions between the two groups will be entered as confounders in all models testing the effectiveness of the intervention. The cluster effect - students are 'nested' in classes - will be handled by getting robust variance-related estimates using procedures for design-based analyses, (cf. [38]). We will correct for the cluster effects at class-level, as the interventions will be carried out in classes. Reporting of the results of the study will be in accordance with the CONSORT statement [39]. Mediation models will be tested with procedures as suggested by MacKinnon et al. [40].

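### The effect models are not tied to the randomisation strata: school is never named and education level enters only if imbalanced, so standard errors are too wide if either predicts outcome

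*Protocol article*

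**What the plan says.** The Randomization section restricts allocation by school and gives the reason: "Randomization will be carried out centrally on class-level and within schools to control for school characteristics". It adds blocks of 2 and stratification by high or low education level.

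The Statistical analysis section makes three statements about the effect models:

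- Nesting of pupils in classes "will be handled by getting robust variance-related estimates using procedures for design-based analyses".
- The level of correction is the class: "We will correct for the cluster effects at class-level, as the interventions will be carried out in classes".
- Covariates follow a rule: "variables that show different distributions between the two groups will be entered as confounders in all models testing the effectiveness of the intervention". The variables checked are "demographic variables (e.g. age, sex, school level, and ethnic background) and depressive symptoms".

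School level is thus a candidate for the imbalance check. School itself appears nowhere in the analysis section.

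**The concern.** Restricted randomisation makes the two arms alike on the blocking factors, so differences between schools or levels largely cancel from the treatment contrast. A class-level robust variance without school or level terms does not see this. It treats the spread of class means across schools and levels as noise in the contrast, although the design has removed it.

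The covariate rule works against the design. It admits a factor because it is imbalanced, and the stratification factors are the ones least likely to be. The factors chosen for the design are therefore the ones the rule tends to keep out.

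Power is at stake, together with the width of the confidence intervals. The trial is planned at 80% power for an effect of 0.20, so there is little room for a test that runs below its nominal level.

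**Working it through.** **The plan's own figure.** The Sample size section starts from this: "Power analysis (G-power) was conducted based on a 12-month effect size of .20". With two-sided alpha 0.05 (sidedness is not stated) and power 0.80, n per arm = 2 × (1.96 + 0.8416)² / 0.20² = 393 after rounding up. Allowing for 20% attrition, 393 / 0.8 = 492 after rounding up. The stated 662 per condition also covers clustering, multiple imputation and mediation, for which no figures are given, so it can be neither confirmed nor called wrong. If clustering explained the whole remaining gap, the design effect would be 662 × 0.8 / 393 = 1.35. At 20 pupils per class that is an ICC of 0.35 / 19 = 0.018. This makes a class ICC of 0.02 a reasonable working value; nothing below depends on 662 being right.

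**Inputs from the protocol.** Total 1,324 pupils, about 25 per class, at most 20% attrition, effect 0.20 (standardised, so SD = 1). Classes: 1,324 / 25 = 53, taken as 52 so that they pair. Analysed pupils per class: 25 × 0.8 = 20.

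**Assumptions.** Class ICC within stratum c = 0.02. Share of total variance between school-by-level strata s = 0, 0.01, 0.02, 0.03 or 0.05. Equal class sizes, arms exactly balanced within strata.

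**Formulas** (variance factor per pupil, 20 pupils per class):

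- As the planned analysis reports it: R = 20(s + c) + (1 − s − c)
- True, given balance within strata: V = 20c + (1 − s − c)
- SE inflation = √(R / V)

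Example at s = 0.02: R = 20 × 0.04 + 0.96 = 1.76; V = 20 × 0.02 + 0.96 = 1.36; √(1.76 / 1.36) = 1.14.

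The last three columns come from simulating 52 classes in strata of 2 or 4, with 1.96 as the critical value for the planned analysis.

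| s | R | V | SE ratio, formula | SE ratio, simulated | Type I error | Power, planned analysis |
|---|---|---|---|---|---|---|
| 0 | 1.38 | 1.38 | 1.00 | 1.00 | 5.6% | 78% |
| 0.01 | 1.57 | 1.37 | 1.07 | 1.06 | 4.2% | 75% |
| 0.02 | 1.76 | 1.36 | 1.14 | 1.13 | 3.1% | 71% |
| 0.03 | 1.95 | 1.35 | 1.20 | 1.19 | 2.4% | 66% |
| 0.05 | 2.33 | 1.33 | 1.32 | 1.31 | 1.3% | 59% |

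With stratum terms and a t reference, type I error stays near 5% and power is about 75–78% across all rows. The 5.6% in the first row comes from using 1.96 with only 52 classes; it has nothing to do with the strata.

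**Power without the simulation.** At s = 0 the true SE is √(4 × 1.38 / 1,040) = 0.0729, where 1,040 = 52 × 20. Then 0.20 / 0.0729 − 1.96 = 0.78, which gives 78%.

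**Sensitivity to c.** With c = 0.015 the simulated SE ratio is 1.13–1.16 at s = 0.02 and 1.33–1.34 at s = 0.05. With c = 0.03 it is 1.10–1.12 and 1.27–1.31.

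**The case against.** The strongest objection is that the omission is read from silence. The sentence on class clustering is correct in itself, since class is the unit of randomisation and of delivery. The protocol never says that school or level will be left out. The imbalance rule is not stated to be the only way into the model. Design-based variance methods can take strata as well as clusters, and the source cited for them is not at hand. A fuller analysis plan might list the strata. Part of this stands: the text does not exclude the strata outright, and education level could enter. But the section does not leave covariates open. It states a selection rule for all the effectiveness models and one level of correction, and that rule does not fit the allocation scheme.

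The objections on size also stand. The between-stratum share is unknown, and at 0 nothing is lost. At about 0.01 the two analyses have similar power. Odd numbers of classes per school would weaken the balance and the effect. Stratum terms cost degrees of freedom, so the comparison has to use a t reference, as above.

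Two stronger readings are tempting. A reader might infer that the blocking is wasted. It is not: it balances the arms and lowers the true variance of the estimate, and only the reported SE, interval and test miss the gain. A reader might also infer that the results would be invalid. The documents do not support that, because ignoring the strata makes the test conservative; it does not create bias or false positives.

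**Conclusion.** The mismatch is real: allocation is restricted by school and education level, and the stated analysis rule commits to neither. The direction is certain if these factors predict outcome: standard errors too wide, type I error below nominal, power lost. The size is conditional. Under the assumptions above, the SE inflation is nil at a between-stratum share of 0 and about 6%, 13%, 19% and 31% at 0.01, 0.02, 0.03 and 0.05. In power, the planned analysis is level with or slightly ahead of the stratified one at 0. It is about 5 points behind at 0.02 (71% against roughly 76%) and further behind above that.

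The documents give no figure for the share. The protocol does describe pupils from vocational to pre-university level and schools of diverse character, and it restricts allocation by school for that reason. This makes a share of exactly zero an odd planning assumption. The point merits a change to the plan but does not threaten the validity of the trial.

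**What to change.** State that school and education level, as randomisation factors, enter the primary and all other effectiveness models as fixed terms whatever the baseline comparison shows. Take them out of the imbalance-driven rule. Keep class as the cluster unit, and use a t reference with degrees of freedom equal to classes minus estimated terms.

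The robust variance needs the matching small-sample correction. If every stratum were a pair, with 25 residual degrees of freedom from 52 equal classes, an uncorrected sandwich variance would be 25 / 52 = 0.48 of the corrected one, and the test would become too liberal.

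No new data are needed. The cost is in degrees of freedom and depends on the number of schools, which is not given. With 26 strata of two classes, 52 − 26 − 1 = 25 remain, about half; with 13 strata of four, 52 − 13 − 1 = 38 remain. If the strata explain no outcome variance, the power loss is about 1–3 points. Separate main effects for school and level, in place of their full combination, limit this cost.
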